## MEDICINE AND MEDICINE HANDLING

### Trial medication

Active drug: **Ropivacaine 5.0 mg/ml.**

Dispensed as a clear colorless fluid for perineural or epidural use. Content: ropivacaine hydrochloride. Furthermore sodium chloride, HCL, sodium hydroxide and water.

Drug import to Denmark: Fresenius Kabi branch of Fresenius Kabi AB, [name]

Owner of the marketing rights: Fresenius Kabi AB. Marketing approval number: 45008.

Does Perineural Clonidine Prolong the Duration of an Adductor Canal Block When  
Controlling for Possible Systemic Effects?  
- A Randomized Paired Trial in Healthy Volunteers  
SM1-JH-14, EudraCT 2014-005640-18, VEK nr SJ-437

Active drug: Clonidine 150 µg/ml

Dispensed as a clear colorless fluid for systemic use. Contains: clonidinehydrochlorid.  
Furthermore HCL (3.6%) (for pH neutralization).  
Water for injection.

Drug import to Denmark: Specifik Pharma

Manufacturer: Boehringer Ingelheim Espana, S.A.

Owner of the marketing rights Germany: 6191514.00.01

Placebo: sodiumchloride 9 mg/ml. Inflation chloride. 1 l contains 9 g sodium chloride in sterile water. Electrolytes/l: 154 mmol chlorid og 154 mmol natrium. Isotonic. Osmolarity approximately 308 mmol/l.

Manufacturer: Skanderborg pharmacy

## **Blinding procedure, packaging and labeling**

The trial is conducted in a blinded, randomized fashion. The randomization is done by a computer generated randomization list, generated by the Skanderborg pharmacy, who according to the randomization manufactures one box for each participant. The trial medicine will be packed and labelled by Skanderborg Pharmacy according to the applicable rules. The individual participant receives the trial medication as stated under "**General treatment plan and medical dosing**".

All participants will receive an ABC with 20 ml of ropivacaine 5 mg/ml in each leg. As this treatment is the same in each leg and accordingly is not blinded, it will be taken from the department's own medical inventory.

Clonidine 150 µg/ml and isotonic saline are both clear, colorless fluids of identical appearance. Clonidine is produced by Boehringer Ingelheim and delivered in clear ampoules marked with a yellow and green line. The same identical empty ampoules are obtained from the manufacturer, and the pharmacy fills them with 1 ml isotonic saline. As the ampoules and content are identical in appearance, clonidine and placebo are blinded and re-labeled by Skanderborg pharmacy, no distinction between the two substances are possible. Each box is packed with 2 x 1.0 mL ampoules, one of which is labeled "RIGHT LEG" and the other labeled "LEFT LEG" and randomization number, containing either clonidine 150 ug ml or placebo, according to randomization. On the trial day, the investigator notes the batch number and expiry, after which the medication is drawn into neutral syringes, labeled RIGHT LEG and LEFT LEG.

Two sets of sealed opaque envelopes are produced, containing information of which treatment the individual participants have received. The sponsor stores one set; the other set is stored by the principal investigator in a locked, safe place at the department of Anesthesiology, Zealand University Hospital, Køge, Denmark.

## **Other treatment**

Other treatment deemed necessary for the participants, will be administered at the discretion of the investigator. The investigator is responsible of all medical decisions related to the trial. All medical treatment will be recorded in the Case Report Form.

## **Procedures in case of emergency**

The Investigator ensures that procedures and expertise exists to manage any emergency that may arise during the trial.

The sealed opaque envelopes containing the assigned treatment can only be opened, if treatment of the participant depends on knowledge of the assigned treatment.

Immediate unmasking can be done without restrictions if deemed necessary without previous contact to monitor or sponsor. If the sealed opaque envelope is broken, date and reason for unmasking is registered in the CRF, and the envelope is signed by the investigator.

## **Medicine handling**

All participant will receive an ACB with 20 ml of ropivacaine 5 mg/ml in each leg. As this treatment is the same in each leg and accordingly is not blinded nor randomized, it will be taken from the department's own medical inventory.

All medicine is handled by an investigator. Each box contains two ampoules; one ampoule containing clonidine and one ampoule of normal saline, for administration according to the labels "RIGHT LEG" or "LEFT LEG".

The investigator mixes the trial medication with 20 ml ropivacaine 0.5% and administers the medication immediately in the relevant legs according to the labels and randomization. Both drugs are clear colorless liquids and will appear identical in appearance and amount.

## **Medicine storage and tracking**

Investigator ensures that the trial medication is kept in a safe place and only administered to participants in this trial. Only the principal investigator will handle the trial medication and batchnumber as well as expiry date will be noted in the trial master file. Investigator accounts for missing medication, as well as any discrepancy between delivered and returned medication.

## **Side effects**

### **Side effects/AEs=adverse events**

Adverse events are defined as any unwanted event, sign or symptom occurring during the trial related to the administration of the trial medication, whether this adverse event is deemed to be related to the trial medication or not. All adverse events are noted in the par-

## Does Perineural Clonidine Prolong the Duration of an Adductor Canal Block When Controlling for Possible Systemic Effects?

- A Randomized Paired Trial in Healthy Volunteers  
SM1-JH-14, EudraCT 2014-005640-18, VEK nr SJ-437

Participants Case Report Form. Should an adverse event occur more than 36 hours after administration of the trial medication, and no apparent association or connection to the trial medication can be made, it is not considered an adverse event.

Beginning and end, severity and symptoms related to the assumed adverse event following administration of the trial medication is noted. The severity of the adverse event and the association to the trial medication is evaluated according to the following guidelines by the investigator.

### **Guidelines for adverse events and causal relations to treatment**

1. Not related – No temporal relation, other causes more likely.
2. Possibly related – Less clear connection, other causes may also be possible.
3. Probably related – Clear temporal connection with clinical improvement after termination of trial medication, and not reasonably explained by the participants known clinical condition.
4. Related – Clear temporal connection with retesting or clinical assessment.

Participants experiencing adverse events will be monitored with relevant clinical assessments and lab tests according to the treating doctor's decision. All adverse events will be followed until satisfactory restitution or stabilization.

A Serious Adverse Event = SAE is an event that leads to risk of death or handicap for the participant (or their offspring) including, but not limiting to, an event that result in:

- Death
- Life threatening circumstance. Participant was, assessed by the investigator, at apparent risk of death by the adverse event as it occurred.
- Hospital admission
- Permanent invalidation
- Innate anomaly

A product resume for clonidine chapter 4.8 and the product resume for Ropivacaine chapter 4.8 from the department of health homepage as a reference document, when assessing whether a serious adverse event is expected or unsuspected.

Reduced sensitivity and motor deficits are a known effect of nerve blocks and will not be reported to the authorities unless strength and sensitivity is not regained within 36 hours after nerve block. There is a known risk of falling when nerve blocks involves n. femoralis, accordingly falling is not seen as an adverse event unless injury occurs in relation to the fall. The risk of falling is probably lower in relation to adductor channel blocks, all possible precautions will be taken to avoid falls.

Bradycardia, hypotension, sedation and dizziness are also known side effects of clonidine and will not be considered an adverse event.

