### **Grading adverse events:**

The investigator is obliged to investigate all clinical and objective reactions among the participants in the trial, and determine any causal relation to the trial medication. Reactions, if any, are graded according to the following scale:

- |   |            |
|---|------------|
| 1 | = light    |
| 2 | = moderate |

Does Perineural Clonidine Prolong the Duration of an Adductor Canal Block When  
Controlling for Possible Systemic Effects?  
- A Randomized Paired Trial in Healthy Volunteers  
SM1-JH-14, EudraCT 2014-005640-18, VEK nr SJ-437

3 = severe  
4 = life threatening

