## Reporting AEs and SAEs

Investigator is responsible for registration of any AEs and SAEs in the participants Case Report Form.

Sponsor is responsible for ongoing monitoring of the trials risk/benefit relations. If events occur that may jeopardize the safety of the participants or the trial, the competent authority should **always** be informed. Similar reporting should also be done to all investigators and ethical committees.

In addition, the following guidelines of reporting to authorities are followed. All events and side effects of the medication are to be reported.

Sponsor is ongoing informed by the investigator on adverse events. By the completion of the trial, the final report should include a description of all adverse events.

Serious Adverse Events – SAE are reported to the sponsor by the investigator immediately. SAE's are reported yearly to the ethics committee during the entire trial period along with a report on the safety of the participants.

Serious adverse reaction – SAR are reported by the sponsor (sponsor-investigator) yearly to the competent authority. The report also entails details on the safety of the participants.

Suspected unexpected serious adverse reaction – SUSAR are reported by the sponsor (sponsor-investigator) to the competent authority and the ethical committee within 24 hours. Report to the competent authority will be done using the electronic form for reporting SUSAR.

Deadly or life-threatening SUSAR's are reported within **7 days** after sponsor's awareness of the event. Within **8 days** of the report, the sponsor must inform the competent authority of all relevant information on the follow-up of the event.

All other unexpected or serious suspected events must be reported to the authorities within 15 days of the event.

Any report to the authorities must be accompanied by a statement on the consequences for the trial.

It is recommended that sponsor (sponsor-investigator) informs the manufacturer of the event.

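### Falls without injury are exempted from adverse events, so the CRF adverse-event record and the final report need not show them; a minor safety-reporting point

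*Protocol*

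**What the plan says.** Under Side effects/AEs=adverse events, the Protocol gives a general definition: "Adverse events are defined as any unwanted event, sign or symptom occurring during the trial related to the administration of the trial medication", and it applies "whether this adverse event is deemed to be related to the trial medication or not". All such events go into the participant's Case Report Form.

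Under Guidelines for adverse events and causal relations to treatment, two exemptions follow. The first concerns falls. After noting that blocks involving the femoral nerve carry a known fall risk, the text says "accordingly falling is not seen as an adverse event unless injury occurs in relation to the fall". The next sentence begins "The risk of falling is probably lower in relation to adductor channel blocks" and ends by undertaking to take precautions against falls. The second concerns the pharmacological effects of the study drug: "Bradycardia, hypotension, sedation and dizziness are also known side effects of clonidine and will not be considered an adverse event".

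Under Grading adverse events, "Reactions, if any, are graded according to the following scale", which runs from 1 (light) to 4 (life threatening). Under Reporting AEs and SAEs, a general sentence says "All events and side effects of the medication are to be reported", and on completion of the trial "the final report should include a description of all adverse events".

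The General treatment plan separately has side effects recorded in the CRF from t=0 until discharge.

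**The concern.** The general definition makes no exception for events that are expected or harmless. The falls clause removes one class of unwanted event from it, and the final report is tied to the term adverse event. A report that follows the protocol to the letter may therefore be silent on an uninjured fall.

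A reader of this trial would want to see such an event. Every participant has both legs blocked at once and also receives 150 µg of clonidine, for which the protocol itself lists hypotension, sedation and dizziness as known effects. In a trial of 21 volunteers the safety description is a short list, and its value lies in being complete.

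The same structure applies to the sentence on bradycardia, hypotension, sedation and dizziness. That exemption has no severity limit, and it covers the effects most likely to lie behind a fall in these participants.

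**Working it through.** The point is one of definitions, so the main check is to set the sections side by side.

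1. **Is an uninjured fall within the general definition?** It is an unwanted event, and if it happens during the trial the definition covers it regardless of attribution. The wording is not perfectly clean, because it mentions a relation to drug administration and then says that relatedness does not matter. The second part is the more specific, so the broad reading is the natural one.

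2. **Does the guideline section remove it?** Yes, explicitly, unless the fall causes injury.

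3. **Does the stated reason call for removal?** The reason is that falling is a known risk of a related block. Under the same guideline section, the product resumes serve to judge whether a serious event is expected. Expectedness therefore has a place in the protocol, but that place is classification and authority reporting, not recording. The protocol also thinks falls less likely with this block, so listing them would cost little.

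4. **Does another line bring falls back?**
   - The recording of side effects in the General treatment plan might. However, the heading Side effects/AEs=adverse events treats the two terms as one, so the exemption may carry over. The text does not settle this.
   - The general sentence under Reporting AEs and SAEs introduces the rules for reporting to authorities, refers to events and side effects of the medication, and does not name falls.
   - The sentence on the final report speaks of adverse events only.

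5. **How do the other exempted effects compare?** The General treatment plan schedules blood pressure every 15 minutes and continuous ECG for 4 hours, and a sedation score every hour. So bradycardia, hypotension and sedation leave a trace in the data. Dizziness, like a fall, has no scheduled reading. All four are outside the final report's adverse-event description in the same way.

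**Illustration of size.** The protocol gives no fall rate, and none is assumed. Suppose one participant of the 21 fell without injury and the fall was left out. Exact (Clopper-Pearson) 95% limits:

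- Reported 0/21: lower limit 0; upper limit 1 − 0.025^(1/21) = 16.1%.
- Actual 1/21 = 4.8%: lower limit 1 − 0.975^(1/21) = 0.1%; the upper limit p solves (1−p)^21 + 21p(1−p)^20 = 0.025, giving 23.8%.

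This shows what one omission would do to the listing. It is not evidence that any fall will occur.

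**The case against.** The strongest reply is that there is no contradiction. A specific, reasoned exception to a general definition is an ordinary drafting device, and this one is stated in plain view. Falls with injury remain adverse events. The protocol promises precautions, describes the block as almost purely sensory with at most a minor motor component, obliges the investigator to investigate all clinical and objective reactions, and requires the authority to be told of anything that may jeopardise safety. All of that stands, and it keeps the point small. None of it puts an uninjured fall into the final report's adverse-event description.

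Four stronger readings are tempting, and the documents do not support them.

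- A reader might infer that uninjured falls will go unrecorded. The text supports only that they need not be recorded as adverse events. The side-effect line in the General treatment plan may still capture them.
- A reader might infer that falls would be missed once continuous monitoring stops at 4 hours. ECG and oximetry do not detect falls, and hourly testing continues afterwards apart from sleep, so the share of blocked time after 4 hours does not measure a detection gap.
- A reader might infer from the 36-hour rule on regained strength that strength goes unassessed, because the named tests are all sensory. The protocol says that motor modalities are tested, the CRF is not shown, and the rule can work on observed or reported weakness. This is operational detail, not an error in the plan.
- A reader might infer that the exemption distorts the comparison of treatments. Both legs are blocked, one with each treatment, so a fall cannot be assigned to either, and no treatment comparison depends on it.

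It is also fair to object that repairing falls alone would be inconsistent: a fall from dizziness would count while the dizziness would not. That objection is accepted, and the fix covers both sentences.

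**Conclusion.** The point holds as a minor matter of safety reporting. The protocol openly exempts uninjured falls from a definition broad enough to include them. As a result, the adverse-event record in the CRF and the final report's description need not show them. The companion exemption for four known clonidine effects has the same consequence for the report, softened for three of them by scheduled measurements.

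The conclusion rests on reading the general definition as independent of attribution and the final-report sentence as limited to adverse events. It assumes no fall rate. What is at stake is the completeness of a safety listing in 21 healthy, observed volunteers. The primary outcome, its analysis and the sample size are untouched.

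**What to change.** In Guidelines for adverse events and causal relations to treatment, delete the falls exception. Every fall from t=0 is then noted in the CRF with injury yes or no, graded on the existing 1 to 4 scale, and described in the final report. The fall should not be assigned to one leg's treatment.

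For consistency, reword the next exemption so that bradycardia, hypotension, sedation and dizziness are recorded and described as expected, non-serious adverse events. An occurrence that meets the protocol's criteria for a serious event would still be handled under those rules.

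The cost is two edited sentences, an injury yes/no entry for each fall, and a few more non-serious events to list. No new assessment, outcome or comparison is needed.

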### Risks, side effects and disadvantages

All procedures, including peripheral nerve blocks, are associated with possible complications, albeit very rarely (0.02-0.4%).

Known complications are:

- Nerve injury (incidence 0.04%). Approximately 99 % of all nerve injuries resolves without treatment within one year.
- Used correctly, no side effects are seen associated with ropivacaine, but upon accidental intravascular injection, serious toxic side effects such as paresthesia, convulsions and circulatory collapse may occur. The risk of intravascular injection of the local anesthetic is minimal, and is reduced by the use of ultrasound and thorough aspiration prior to and after every 5 ml of local anesthetic.
- Systemic side effects of clonidine are transient and often mild. Sedation is normally not perceived as unpleasant. Hypotension (MAP <55) can be treated by administering isotonic saline or ephedrine 10 mg. Bradycardia can occur, but rarely requires treatment. Significant bradycardia of HR<40 can be treated with atropine 0.5 mg iv.
- A small hematoma can occur at the needle puncture site. This may cause tenderness but resolves without treatment.

The nerve blocks will be performed using ultrasound guidance, which probably reduces the risk of complications.

There is a dose response relationship between clonidine and the prolongation of the nerve block. Most studies with positive results used a dose of 150 µg, and at the same time reports a minimum of side effects (30). Clonidine is used frequently daily at the hospital for the treatment of shivering on recovery wards after surgery and opioid abstinence in the ICU. At doses of 300 micrograms, more significant sedation and hemodynamic instability is observed (30).

A peripheral venous catheter is inserted, which rarely leads to a stinging sensation and a small hematoma after removal.

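### Four known clonidine effects are exempted from adverse event status without any limit, contradicting the protocol's own adverse event definition and its grading and reporting rules

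*Protocol*

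**What the plan says.** The section Side effects/AEs=adverse events gives a broad definition: "Adverse events are defined as any unwanted event, sign or symptom occurring during the trial related to the administration of the trial medication", continuing "whether this adverse event is deemed to be related to the trial medication or not". Such events go into the case report form with their start, end, severity and symptoms, and the investigator judges severity and causality.

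The next section, Guidelines for adverse events and causal relations to treatment, lists four causality categories and requires adverse events to be followed until they resolve or stabilise. It closes with an exemption: "Bradycardia, hypotension, sedation and dizziness are also known side effects of clonidine and will not be considered an adverse event". The only ground given is that the effects are known.

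Three other places bear on the point:

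- Grading adverse events obliges the investigator to look into every clinical and objective reaction, decide on causality and grade it from 1 to 4.
- Reporting AEs and SAEs says that events and side effects of the medication are all to be reported. It later says that "the final report should include a description of all adverse events".
- Risks, side effects and disadvantages says "Systemic side effects of clonidine are transient and often mild". It then discusses sedation, hypotension and bradycardia, and foresees that the last two may be treated.

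**The concern.** Whether an effect is already known bears on expectedness, that is, on how a serious reaction is classified for reporting. It does not decide whether something that happened to a participant is an adverse event. The guidelines section already gives known effects their proper use: it names section 4.8 of the two product resumes as the reference for judging whether a serious event was expected. The exemption uses the same attribute for a different purpose, to remove events from the category altogether.

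What is at stake is the descriptive safety record. Every participant is a healthy volunteer who, by the protocol's own account, gains no direct benefit. Each receives clonidine perineurally, a use for which the ethical considerations say it is not approved. A safety description that leaves out the most foreseeable effects of the study drug would tell later readers little about what they most need to know.

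**Working it through.** No arithmetic applies. The point rests on definitions and reporting rules and does not depend on the sample size, error rates or effect size. The check sets the provisions side by side.

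**1. Definition against exemption.** The definition covers "Adverse events are defined as any unwanted event, sign or symptom occurring during the trial", whatever the judged causality, and contains no carve-out for known effects. An unwanted episode of hypotension after the block meets it. The exemption says the same episode is not an adverse event. Both cannot hold.

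**2. Is the exemption limited?** Two neighbouring exemptions in the same section are.

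| Effect | What is exempted | Limit |
|---|---|---|
| Reduced sensitivity and motor deficit | Reporting to authorities only: "will not be reported to the authorities unless strength and sensitivity is not regained within 36 hours after nerve block" | Time |
| Falls | Adverse event status: "falling is not seen as an adverse event unless injury occurs in relation to the fall" | Injury |
| Bradycardia, hypotension, sedation, dizziness | Adverse event status | None |

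The clonidine exemption has no limit of severity, duration, treatment or seriousness. Yet the risks section foresees that hypotension (MAP below 55) and bradycardia (HR below 40) may be treated. Read literally, even a treated episode is not an adverse event.

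**3. What depends on adverse event status?** Four things: the record of onset, end, severity and causality under the definition; follow-up to resolution or stabilisation; ongoing information to the sponsor; and the description in the final report. On the wording of the exemption, the four effects lose their claim to each of these as adverse events.

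**4. What does not depend on it?**

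- The trial schedule keeps continuous ECG, pulse oximetry and 15-minute blood pressure for 4 hours, and hourly sedation scores from 0 to 3.
- It also has side effects entered in the case report form until discharge.
- Other treatment requires all medical treatment to be recorded there.
- Grading adverse events is worded in terms of reactions, so its causality and grading duty can be read to cover the four effects.
- A serious adverse event is introduced as an event, not as an adverse event.

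The source data therefore survive. The classification and the commitment to describe these effects do not survive unambiguously.

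**5. Which effects, and how many participants?** The risks section lists sedation, hypotension and bradycardia as clonidine effects. Dizziness appears only in the exemption. All participants receive both treatments, one in each leg, so all 21 planned participants are exposed to clonidine.

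**The case against.** The best defence is that the protocol handles these effects elsewhere. They are expected pharmacology, they are monitored directly, side effects and treatments are entered in the case report form, and the reporting section asks for all side effects of the medication to be reported. On that view the exemption only avoids listing the same finding twice.

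Much of this stands, and it rules out three stronger readings that a reader might infer:

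- **That the effects receive no grading or causality assessment.** The grading section attaches that duty to all reactions, although its heading speaks of adverse events.
- **That they could never count as serious.** The definition of a serious adverse event speaks of an event and lists hospital admission, and the reporting section requires the competent authority to be told of events that may jeopardise participants' safety. For these four effects the text is ambiguous; it is not a bar.
- **That they would be wholly missing from the safety record.** The monitoring data, the side effect entries and the treatment entries all remain, and the reporting section's sentence on side effects argues against total omission.

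It is also fair to say that the outcomes section names no safety outcome. Since every participant receives clonidine, systemic events cannot be compared between treatments in any case.

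The defence does not remove the contradiction. The general sentence on reporting side effects introduces the rules on reporting to authorities, and the sentence that fixes the final report's content is confined to adverse events. With no safety outcome listed, nothing else clearly commits the report to describing these effects. If they were meant to be reported separately from adverse events, the protocol would have to say so, and it does not.

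**Conclusion.** The point holds as an internal contradiction with a bounded consequence. The exemption cannot be reconciled with the adverse event definition and is inconsistent with the grading and reporting sections. If it is followed as written, four effects leave the adverse event count, the adverse event follow-up and the final report's description of adverse events. Three of the four are the systemic clonidine effects that the protocol itself discusses.

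The size is qualitative. The protocol gives no incidence for any of the four effects, so the number of events affected cannot be estimated from it. What is lost is the description of how often and how severely these effects occur in up to 21 exposed volunteers. The primary and secondary efficacy analyses are untouched.

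The conclusion assumes that the exemption would be applied literally. An investigator who relied on the grading and reporting sections instead could reach a fuller safety account. That two readers can arrive at different adverse event lists from the same protocol is itself the defect.

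**What to change.** Reconcile the definition, guidelines, grading and reporting sections by deleting the exemption sentence. Then:

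- record bradycardia, hypotension, sedation and dizziness as adverse events, using the protocol's existing four causality categories and its grades 1 to 4;
- describe them in the final report, stating which were treated;
- keep known-effect status only for judging the expectedness of serious events, against the product resumes that the protocol already names.

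No dose, treatment threshold or management rule changes, and no new measurement is needed. Bradycardia, hypotension and sedation are covered by the scheduled monitoring, although ECG and 15-minute blood pressure are specified for 4 hours only. Dizziness is captured only through the side effect entries in the case report form.

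The costs are a higher reported adverse event count and some extra recording. Deletion alone also leaves open when a monitored reading counts as an unwanted event. The sponsor should state how that is decided; no criterion is proposed here.
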